## Abstract

The COVID-19 pandemic and its related containment measures—mainly physical distancing and isolation—are having detrimental consequences on the mental health of the general population worldwide. In particular, frustration, loneliness, and worries about the future are common reactions and represent well-known risk factors for several mental disorders, including anxiety, affective, and post-traumatic stress disorders. The vast majority of available studies have been conducted in China, where the pandemic started. Italy has been severely hit by the pandemic, and the socio-cultural context is completely different from Eastern countries. Therefore, there is the need for methodologically rigorous studies aiming to evaluate the impact of COVID-19 and quarantine measures on the mental health of the Italian population. In fact, our results will help us to develop appropriate interventions for managing the psychosocial consequences of pandemic. The “COVID-IT-mental health trial” is a no-profit, not-funded, national, multicentric, cross-sectional population-based trial which has the following aims: a) to evaluate the impact of COVID-19 pandemic and its containment measures on mental health of the Italian population; b) to identify the main areas to be targeted by supportive long-term interventions for the different categories of people exposed to the pandemic. Data will be collected through a web-platform using validated assessment tools. Participants will be subdivided into four groups: a) Group 1—COVID-19 quarantine group. This group includes the general population which are quarantined but not isolated, i.e., those not directly exposed to contagion nor in contact with COVID-19+ individuals; b) Group 2—COVID-19+ group, which includes isolated people directly/indirectly exposed to the virus; c) Group 3—COVID-19 healthcare staff group, which includes first- and second-line healthcare professionals; d) Group 4—COVID-19 mental health, which includes users of mental health services and all those who had already been diagnosed with a mental disorder. Mental health services worldwide are not prepared yet to manage the short- and long-term consequences of the pandemic. It is necessary to have a clear picture of the impact that this new stressor will have on mental health and well-being in order to develop and disseminate appropriate interventions for the general population and for the other at-risk groups.

## Background

The ongoing COVID-19 pandemic represents an unprecedented event in terms of consequences for physical and mental health of individuals and for the society at large (1–4). In order to reduce the spread of the virus, national and international bodies and institutions have ordered quarantine, physical distancing, and isolation almost everywhere in the world. However, the psychological consequences of quarantine, such as frustration, loneliness, and worries about the future are well-known risk factors for several mental disorders, including anxiety, affective disorders, and psychoses (5–7).

From a medical and sociological viewpoint, the pandemic caused by COVID-19 represents a unique event, since it does not resemble any other previous traumatic event, such as earthquakes or tsunamis (8). In those cases, the traumatic factors are usually limited to a specific area and to a given time; affected people know that they can “escape” from the event. On the contrary, in the case of COVID-19 pandemic, the “threat” can be everywhere and can be carried by every person next to us (9–11). Therefore, people living in cities most severely impacted by the pandemic are experiencing extremely high levels of uncertainties, worries about the future and fear of being infected.

The only comparable studies are those carried out during the SARS outbreak (12–16). Those studies showed that people experienced fear of falling sick or dying, feelings of helplessness, increased levels of self-blame, fear, and depression (17–20). During quarantine and physical distancing, Internet and the social media can be useful in reducing isolation and increasing opportunities to keep in contact with family members, friends, and co-workers at any time (21, 22). However, Internet may also represent a risk factor for mental disorders, in particular Internet Gaming Disorder. Moreover, Internet can also have a negative impact on mental health of the most vulnerable people, such as those who live alone or the elderly, since it spreads an uncontrolled amount of information (a situation known as “infodemic”).

In the current pandemic, the impact of quarantine and physical distancing on the mental health of the general population has been explored only in a few studies, mostly conducted in China, where the pandemic started (23–25). Qiu et al. (26) found that 35% of the population experienced psychological distress; in particular, those more vulnerable to stress and more likely to develop post-traumatic stress disorder were women and individuals aged between 18 and 30 years or older than 60 years. Moreover, people were more concerned about their own health and that of their family members, while less concerned about leisure activities and relationships with friends (24, 27).

After China, Italy has been the first country to face the contagion of COVID-19 and one of the countries with the highest number of deaths due to this coronavirus (http://www.salute.gov.it/portale/nuovocoronavirus/). On March 8, the lockdown status has been declared by the Italian government. This status included the definition of specific containment and quarantine measures, such as the interdiction of all public meetings and strict movement restrictions (i.e., possibility to go out only for working, serious health reasons, or other urgent needs). These containment measures have been prolonged until May 4.

Moreover, the expected psychosocial and emotional reactions to the pandemic observed in the general population may be significantly different in the Chinese and Italian populations due to their socio-cultural characteristics and historical contexts, which obviously impact on people’s behaviors and attitudes. Furthermore, the organization of public health system is different in Italy compared to China and other Eastern Asian countries, also due to financial constraints. In fact, although in those countries the model of care has shifted in the last 20 years to become more similar to a Western model of care, it has to be acknowledged that 20 years is a relatively short period of time, and differences may still persist.

Methodologically rigorous studies are needed in order to evaluate the impact of COVID-19 and quarantine measures on the mental health of Italian population. These data will help us to develop appropriate interventions for managing the psychosocial consequences of the pandemic (28–30). The present study has been developed with the aims to: a) evaluate the impact of COVID-19 pandemic and its containment measures on mental health of the Italian population; b) to identify the main areas to be targeted by supportive long-term interventions for the different categories of people exposed to the pandemic.

## Methods

### Design

The “COVID-IT-mental health trial” is a no-profit, not-funded, national, multicentric, cross-sectional population-based trial involving the following eleven sites: University of Campania “Luigi Vanvitelli” (Naples), Università Politecnica delle Marche (Ancona), Università Milano Bicocca, Università “Statale” (Milan), University of Perugia, University of Pisa, Sapienza University of Rome, “Cattolica” University of Rome, University of Trieste, University of Ferrara; the Center for Behavioral Sciences and Mental Health of the Istituto Superiore di Sanità (Rome). The Department of Psychiatry of the University of Campania “Luigi Vanvitelli” in Naples is the coordinating center, which has originally conceived the study idea and design.

### Data Collection

#### Recruitment Procedure

An online survey has been set up through EUSurvey, a web platform launched in 2013 by the European Commission. The application, hosted at the Department for digital services (DG DIGIT) of the European Commission, is available to all EU citizens at https://ec.europa.eu/eusurvey. The survey will be online from March 30 to June 30, 2020 (https://ec.europa.eu/eusurvey/runner/COVIDSurvey2020). The survey takes approximately 15–30 min to be completed. Participants can stop the survey at any time and save their answers as “draft” on the web-platform. Furthermore, participants can interact with the principal investigator of the study and with all researchers through email messages at any time during and after study participation.

Participants will be subdivided into four groups: a) Group 1—COVID-19 quarantine group. This group includes the general population which are quarantined but not isolated, i.e., those not directly exposed to contagion nor in contact with COVID-19+ individuals; b) Group 2—COVID-19+ group, which includes isolated people directly/indirectly exposed to the virus; c) Group 3—COVID-19 healthcare staff group, which includes first- and second-line healthcare professionals; d) Group 4—COVID-19 mental health, which includes users of mental health services and all those who had already been diagnosed with a mental disorder.

The survey addresses the Italian population aged over 18 years through a multistep procedure: 1) email invitation to health professionals and their patients; 2) dissemination of the link through social media channels (Facebook, Twitter, Instagram) and the mailing lists of national psychiatric associations; 3) involvement of national associations of stakeholders (e.g., associations of users/carers); 4) official communication channels (e.g., university websites; websites of the hospitals directly involved in the management of the pandemic).

The invitation letter includes information on study purposes and confidentiality. The provision of the informed consent is mandatory in order to start the survey.

The snowball sampling procedure—without the definition of strict inclusion/exclusion criteria (except that of age limit)—will give us the opportunity to recruit a large sample of the Italian population and to evaluate the effect of the studied variables on the outcome measures.

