### Outcomes

#### Primary Outcome

The primary outcome of the study is the global score at the DASS-21. This choice is due to the fact that this assessment measure has already been used in a large population study carried out in China, thus giving us the opportunity to compare the Italian situation with the Chinese one (45). Our study hypothesis is that the pandemic and the related containment measures are associated with higher levels of depressive and anxiety symptoms in the surveyed population compared to a community Italian sample not exposed to the pandemic (46). Furthermore, a significant difference between groups will be identified (COVID-19 quarantine group = COVID-19 healthcare professional second-line < COVID-19+ group = COVID-19 healthcare professional first-line group < COVID-19 mental health group).

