Another possible limitation of our study is the choice to use a web-based online survey, which may have limited the participation of people not having access to the Internet or not familiar with online tools, particularly the elderly. The cross-sectional design of the study does not allow an evaluation of changes over time as regards the levels of severity of symptoms. However, in order to overcome this possible bias, we will compare our findings with those already available from the Italian population (46) and will adopt a propensity score approach in order to understand the impact of the duration of exposure to the pandemic on the risk of developing psychiatric symptoms. With this methodology, we will be able to evaluate the levels of post-traumatic growth and the type of resilience styles in the study population in order to identify possible critical areas to be targeted in the post-acute phase. However, these psychological constructs are slow to change, and this is why we will promote a second wave of the survey, which will start six months after the end of the “lockdown phase” in Italy. Finally, the survey link can be used multiple times in order to allow sharing and re-posting it. This methodological choice could bias the findings, since the same person can potentially compile the survey several times. However, this methodological choice was due to the adoption of the “snowball” sampling, and it is rather unlikely that someone can compile the same long survey more than once.

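### The survey window runs 57 days past the stated end of containment, and neither the Group 1 criterion nor the propensity model distinguishes answers given before and after that date

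*Protocol article*

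**What the plan says.** **Dates.** The Background places the start of lockdown on March 8 ("On March 8, the lockdown status has been declared by the Italian government") and then says: "These containment measures have been prolonged until May 4". Under Recruitment Procedure, "The survey will be online from March 30 to June 30, 2020".

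**Group 1.** Recruitment Procedure describes it in the present tense: "This group includes the general population which are quarantined but not isolated". The explanatory clause that follows narrows it to "those not directly exposed to contagion nor in contact with COVID-19+ individuals". Sampling is by snowball, "without the definition of strict inclusion/exclusion criteria (except that of age limit"). No stated rule uses the response date or whether the respondent is under quarantine when answering.

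**Analysis.** Data Analysis plans a propensity score for the likelihood of exposure to the pandemic and to the quarantine. It is built from gender, age, socio-economic status and region, and is used as inverse probability weights to estimate causal effects. The confounders named at the end of that section are age, gender and region. Exploratory Outcomes lists time exposed to COVID-19 and to containment as a possible mediator. The Discussion says the propensity approach will help to understand the effect of duration of exposure.

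**The concern.** Read against the stated dates, Group 1's label and its working criterion diverge after May 4. A member of the general population who answers in June, with no exposure or contact, meets the criterion but may not be quarantined. Such answers are pooled with those given under lockdown, and nothing in the listed analysis separates the two.

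Two results are at stake. First, any estimate presented as the effect of quarantine would average over people who were and were not quarantined. Second, recruitment uses several channels (email to professionals and patients, social media, associations, institutional websites), and these may reach the four groups at different times. If they do, a difference between groups partly reflects a difference in calendar phase. Loneliness, a secondary outcome for Group 1, plausibly depends on confinement.

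**Working it through.** The article gives no power or sample-size calculation on this point, so there is no figure to reproduce. The check is date arithmetic followed by bounds.

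**1. Calendar days (dates from Background and Recruitment Procedure)**
- March 30 to June 30 inclusive: 2 + 30 + 31 + 30 = 93 days.
- March 30 to May 4 inclusive: 2 + 30 + 4 = 36 days.
- May 5 to June 30: 27 + 30 = 57 days.
- 57 / 93 = 61% of calendar time.

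**2. Share of respondents after May 4**

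The Discussion reports 10,000 participants reached in 7 days and expects more than 20,000. Assume that those were the first 7 days and that the total is 20,000. The other 10,000 then arrive over 93 − 7 = 86 days.
- Even later accrual: 10,000 × 57 / 86 = 6,628, and 6,628 / 20,000 = 33%.
- Accrual halving each week: 2^(−36/7) = 0.028, about 3%.
- Upper bound, all the rest after May 4: 10,000 / 20,000 = 50%.
- With 30,000 in total, even accrual gives 20,000 × 57 / 86 = 13,256, or 44%, and the upper bound is 67%.

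These shares are for all respondents. The article gives no accrual by group.

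**3. Effect on a pooled estimate**

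Let f be the share answering after May 4 and r the effect after May 4 relative to the effect before it. The pooled effect, as a fraction of the lockdown effect, is 1 − f(1 − r).

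| f | r = 0 | r = 0.5 | r = 1 | r = 1.2 |
|---|---|---|---|---|
| 3% | 0.97 | 0.985 | 1.00 | 1.006 |
| 33% | 0.67 | 0.835 | 1.00 | 1.066 |
| 50% | 0.50 | 0.75 | 1.00 | 1.10 |

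The article gives no value for r. The pooled figure is too small if r < 1, unaffected if r = 1, and too large if r > 1.

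**4. Effect on a group contrast**

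Suppose mean scores shift by δ after May 4 in both groups, and the late shares are f_A and f_B. The crude difference is then off by (f_A − f_B) × δ. As an illustration only, taking two of the accrual patterns above, f_A = 33% and f_B = 3% give 0.30 × δ. If the shares are equal, this error is zero.

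**5. Whether the plan already removes the error**

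None of the four propensity variables or three named confounders carries date or phase. Exposure time is an exploratory mediator, which does not adjust the primary comparison. The mediators and moderators listed for the structural equation model (coping, post-traumatic growth, social network use) do not include it. Duration is also not the same as phase: after May 4, time in the pandemic continues while time under containment may not.

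**The case against.** The strongest case against the point is that late respondents are not unexposed. The aim covers the pandemic as well as its containment measures, and the primary hypothesis sets the surveyed population "compared to a community Italian sample not exposed to the pandemic". A June respondent belongs in that comparison. The explanatory clause and the Discussion's description of Group 1 (general population not directly affected by the virus) also still admit that person. This stands, and it is why late answers should be kept.

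A reader might infer several stronger things that the article does not support:
- **That the late window dilutes the effect.** Nothing says symptoms fall after May 4. The Discussion expects the burden on ordinary life to grow the longer the pandemic lasts, and the table above gives dilution only for r < 1.
- **That 61% of the sample is affected.** That is calendar time, and early accrual was fast.
- **That Group 1 is the reference for every contrast.** Primary Outcome states an ordering without a reference group, and Secondary Outcomes includes a first-line versus second-line staff comparison that does not involve Group 1.
- **That the planned later wave shows this one is meant only for lockdown.** The article does plan "a second wave of the survey, which will start six months after the end of the" lockdown phase, but the reason it gives is that growth and resilience change slowly.
- **That all restrictions ended on May 4.** The article gives an end date as then set and says no more.

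It can also be said that modelling by response week is detail for an analysis plan, and that the remarks on exposure time and duration show time was considered. The first has some force, but the article does name its groups, covariates and confounders, and these do not fit its survey window. The second does not close the gap, because no listed covariate carries time.

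**Conclusion.** The point holds in limited form. The stated dates, the Group 1 label and the covariate list do not fit together: 57 of 93 survey days follow the stated end of containment, the working criterion admits respondents from both phases, and no listed adjustment separates them. Estimates attributed to quarantine mix two exposure states, and group contrasts are open to confounding with calendar phase if accrual differs between groups.

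Neither the direction nor the size of the error can be fixed from the article. Under the assumptions of 10,000 in the first 7 days and 20,000 in total, the affected share is about 33% with even later accrual, about 3% with weekly halving, and at most 50%; a larger total raises the even-accrual figure and the maximum. The comparison of the whole surveyed population with the unexposed community sample is less affected, since late respondents remain exposed to the pandemic. The article does not support a claim of bias toward no effect, or removing late respondents from the primary analysis. This is an inexpensive improvement to the analysis, not a flaw that invalidates the study.

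**What to change.** 1. State that Group 1's quarantine status refers to the time of response.
2. Use the submission date to define period (up to May 4 versus after) or response week, and add it to the propensity and regression models. Where the modelled exposure is quarantine itself, period may nearly determine it and make the weights unstable; in that case rely on the results by period.
3. Report Group 1 and between-group results by period, with the number of respondents per group and period, so that differences in accrual are visible.
4. Add a sensitivity analysis restricted to responses up to May 4. Keep later responses in the study as pandemic-exposed data.

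**Cost.** Changes to analysis wording, slightly more analysis, and smaller numbers per period. No new data collection is needed, assuming the survey platform stores submission dates, which the article does not say. If the 10,000 came in the first 7 days, the period up to May 4 already holds the article's ideal target overall. Group sizes are not given, so precision within the smaller groups should be checked before the period results are interpreted.

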#### Secondary Outcomes

In the COVID-19 quarantined group, the severity of obsessive-compulsive symptoms, evaluated through the OCI-R, the perceived loneliness and suicidal ideation will be considered as secondary outcome measures.

In the COVID-19+ patient group, the severity of post-traumatic symptoms at the Severity-of-Acute-Stress-Symptoms-Adult scale will be considered. The hypothesis is that post-traumatic symptoms are more severe in this group compared to the other ones.

In the COVID-19 health staff group, the presence of burn-out symptoms, in particular mental exhaustion, and suicidal ideation will be considered. We anticipate that first-line professionals will report higher levels of mental exhaustion and suicidal ideation compared to second-lines staff members.

In the COVID-19 mental health group, the secondary outcome measures will include the adoption of maladaptive coping strategies (e.g., drinking alcohol) and a poor resilience style. Patients with pre-existing mental disorders are expected to adopt more maladaptive coping strategies and poorer resilience styles compared to the other three groups.

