## Discussion

Our survey will give us the opportunity to describe the impact of the pandemic on the mental health of different subgroups of the Italian population.

In fact, the analyses will be run according to the four subgroups of respondents: the general population not directly affected by the virus (COVID-19 quarantine group); people who have had a direct or indirect contact with the virus (COVID-19+ patients group); those working in health care units as first or second-line staff (COVID-19 healthcare staff group); people with mental health problems, independently from the contact with the virus (COVID-19 mental health). This choice is due to the evidence that stress and traumas have a different impact on different target groups (7, 50–52).

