In the COVID-19-quarantine group, we anticipate that the pandemic and the related containment measures will increase the levels of stress, anxiety and depression, as well as other stress-related symptoms. In particular, physical distancing has obviously changed the patterns of daily routine in order to mitigate the spread of the disease, with serious consequences on mental health and well-being in both the short- and long-term (53). Similar consequences would require immediate efforts for developing preventive strategies as well as direct interventions aiming to mitigate the impact of the outbreak on individual and population mental health. The longer the pandemic will last the most the ordinary life of the general population will be seriously affected. In particular, Zhang et al. (23) have highlighted the need to pay attention to the mental health of people who have not been directly infected by the virus though have been forced to stop all their activities during the outbreak. These people represent the most susceptible group to the detrimental impact of quarantine and physical distancing measures adopted during the lockdown. Moreover, during the current pandemic, it is reasonable to expect that the incidence of severe mental disorders will increase, but also that of other mental health disturbances not reaching the threshold for a full-blown diagnosis (3). However, currently available data are based on studies carried out in China and the different socio-cultural context may limit the generalizability of findings to the Italian and Western contexts. Therefore, we consider essential to collect Italian data in order to develop data-driven guidelines for an adequate management of mental health problems during the emergency and the post-emergency phases. In fact, this survey will represent the starting point for developing, validating, and implementing psychosocial supportive interventions (53, 54), as discussed later in this paper.

We hypothesized that Internet and social media can play a buffering role in the development of psychiatric symptoms (25, 55). It may be that online contacts and interactions will limit the detrimental effects of social isolation (56). Moreover, Internet can represent the ideal setting for providing supportive interventions through tele-mental health applications (57–60). However, the positive effect of Internet and social media has to be confirmed yet, since it is only speculative at this stage.

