Finally, the pandemic will affect the mental health status of people who already suffer from mental health problems, independently from the contact with the virus (COVID-19 mental health group). Although the effects of the coronavirus on mental health have not been systematically studied, it is likely that the COVID-19 will have detrimental effects on patients with pre-existing mental health problems. Many patients with severe mental disorders have been overlooked during the pandemic, although they can have a higher risk of contracting the virus and of death considering the higher prevalence of somatic comorbidities compared to general population and the difficulties in accessing health services (70).

However, if protracted, social isolation may increase the risk of recurrences of episodes of mental disorders, beyond triggering the onset of new mental disorders in most vulnerable people. Moreover, objective social isolation and subjective feelings of loneliness are associated with a higher risk of suicidal ideation and suicide attempts (71). For many persons with mental disorders, being alone is a heavy burden, far beyond that experienced by many other persons (72).

In patients with pre-existing anxiety disorders or obsessive-compulsive disorder, we expect an exacerbation or worsening of their clinical symptoms. Moreover, the fact that there is not (yet) a definitive treatment for the COVID infection represents another potential stressor, further increasing the levels of anticipatory anxiety and reducing personal functioning. In our study, both obsessive-compulsive and anxiety symptom clusters will be evaluated through reliable and validated questionnaires.

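### Group 4 is read as pre-existing mental disorder, but its service-user limb has no pre-pandemic cut-off, so people who first entered care because of the pandemic qualify

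*Protocol article*

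**What the plan says.** Recruitment Procedure divides participants into four groups. Group 4 is the one "which includes users of mental health services and all those who had already been diagnosed with a mental disorder". The first limb (service users) has no date. The second uses the word already but names no reference point. Of Group 1 the same section says: "This group includes the general population which are quarantined but not isolated". It does not mention mental health care, past or current, and it gives no order of precedence for someone who fits two groups.

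Secondary Outcomes tests Group 4 as prior illness: "Patients with pre-existing mental disorders are expected to adopt more maladaptive coping strategies and poorer resilience styles compared to the other three groups". The Discussion also speaks of people already ill, but its summary of the four groups lists only "people with mental health problems, independently from the contact with the virus (COVID-19 mental health".

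On timing, Background states: "On March 8, the lockdown status has been declared by the Italian government". Recruitment Procedure states: "The survey will be online from March 30 to June 30, 2020". The Discussion anticipates new illness in this period. It says "it is reasonable to expect that the incidence of severe mental disorders will increase", and that prolonged isolation may worsen existing illness, "beyond triggering the onset of new mental disorders in most vulnerable people".

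Data Analysis treats the four groups as levels of exposure to the pandemic. It builds the propensity score from age, gender, region and socio-economic status; psychiatric history is not listed.

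**The concern.** The rule and its use do not match. Suppose a person with no psychiatric history becomes depressed during lockdown, contacts a mental health service in April and answers in May. That person is a service user when answering and meets the first limb of Group 4. Membership can then be a consequence of the exposure under study.

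Two things are at stake. First, the coping and resilience hypothesis for pre-existing disorders would be tested on a mixture of long-standing and new cases. Second, if such people are counted only in Group 4, Groups 1 to 3 lose some of their newly ill members. Their DASS-21 results, and secondary results such as suicidal ideation and obsessive-compulsive symptoms, would then look milder than they are. Weighting on the listed propensity covariates cannot repair this, because none of them separates illness before the pandemic from illness after it began.

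**Working it through.** **Can the gap be filled by real respondents?** March 8 to March 30 is 22 days, and March 8 to June 30 is 114 days. Every respondent answers between day 22 and day 114 of lockdown exposure, so first contact with a service after March 8 is possible for all of them. Recruitment goes partly through health professionals' patients and user associations, so people in care are directly sought.

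**Size.** The plan gives no figure to reproduce and none of the inputs needed. The following is illustration under assumed values. In an exposure group, let
- c = share made ill by the pandemic;
- D = their excess score, in SD;
- s = shift common to everyone, in SD;
- q = share of the newly ill who are in care or diagnosed when they answer, and so move to Group 4.

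True shift = s + cD. Observed shift after the move = s + c(1 − q)D / (1 − cq).

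With D = 1, c from 5% to 20% and q from 5% to 50%:

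| s | Hidden, SD | Hidden, % of true shift |
|---|---|---|
| 0 | 0.002 to 0.089 | 4% to 49% |
| 0.2 | 0.002 to 0.089 | 1% to 22% |

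**One worked case.** Assume 9,000 people in Group 1 (c = 10%, q = 30%, D = 1, s = 0) and 1,000 true prior cases with mean 1.2 SD.
- Moved: 9,000 × 0.10 × 0.30 = 270.
- Group 1 mean: 900/9,000 = 0.100 before; (900 − 270)/(9,000 − 270) = 630/8,730 = 0.072 after.
- Group 4 mean: 1.20 before; (1,200 + 270)/1,270 = 1.16 after. New cases are 270/1,270 = 21% of it.
- Pooled mean: (900 + 1,200)/10,000 = 0.21 before; (630 + 1,470)/10,000 = 0.21 after.

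**A second set of assumptions.** Take 15,000 people who meet Group 1 and 1,500 true prior cases. Let 2% to 5% of the 15,000 newly contact services and score 1.5 SD above the rest. Then 300 to 750 move. They form 300/1,800 = 17% to 750/2,250 = 33% of Group 4. The Group 1 mean falls by 0.02 × 1.5 = 0.03 to 0.05 × 1.5 = 0.075 SD.

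**Contrast between exposure groups.** With c = 20% in Group 2 and 5% in Group 1 (D = 1, s = 0), the true difference is 0.150 SD. At q = 10% it becomes 0.18/0.98 − 0.045/0.995 = 0.138. At q = 30% it becomes 0.14/0.94 − 0.035/0.985 = 0.113.

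**The case against.** The intent is clear: the second limb, the secondary hypothesis and most of the Discussion all point to prior illness. The Discussion's shorter summary is a one-line restatement whose qualifier concerns virus contact, so it should not be read as deliberately widening the group. An article may also leave the exact survey item to the full protocol. This stands in part. Whether onset date is captured is unknown: Table 1 describes the care schedule as covering treatments received, and its items are not shown. But the grouping rule itself is stated, and as stated its first limb does not carry the intent.

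The loss from Groups 1 to 3 needs exclusive groups with Group 4 taking precedence, and no such rule is written. This also stands. Subdivision into four groups and comparison with the other three imply exclusivity. The Discussion supports precedence over virus contact. Nothing settles it for healthcare staff. If people could count in two groups, Groups 1 to 3 would lose nothing, though Group 4 would still be mixed.

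A reader might infer that everyone made ill by the pandemic leaves the exposure groups. The rule does not do that: only those who reached care or a diagnosis before answering can move, and the Discussion notes that access to services was difficult.

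A reader might also infer a bias that grows steadily to the end of June. The protocol reports 10,000 responses within 7 days and expects more than 20,000. If those were the first 7 days, that is by about April 6, roughly day 29, so up to about half (10,000/20,000) answered when few new cases could have reached a service.

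**Conclusion.** The point holds for the undated service-user limb. As written, Group 4 admits people whose first contact with care resulted from the pandemic, while the plan tests and interprets it as pre-existing disorder. That contamination follows from the text and the dates. The understatement of group-level results in Groups 1 to 3 follows only if Group 4 takes precedence, and if those who move score above the rest of their group.

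The size cannot be derived from the documents. The assumed examples give reductions of 0.03 to 0.075 SD in the Group 1 mean, and new cases as 17% to 33% of Group 4. Those shares apply one rate to the whole sample and so ignore the early concentration of responses. The effect is probably modest.

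A reader might infer that the headline finding on the Italian population is biased. The documents do not support this. The first primary hypothesis compares the surveyed population as a whole with an unexposed community sample, and moving people between groups leaves a pooled mean unchanged (0.21 SD either way in the example). The fault concerns the between-group primary hypothesis, the group-specific secondary outcomes and the reading of Group 4. It is worth correcting but does not undermine the study.

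**What to change.** - Define Group 4 as a diagnosis of a mental disorder, or use of mental health services, that began before March 8, 2020. Use the same wording in Recruitment Procedure, Secondary Outcomes and the Discussion summary of the groups.
- State the precedence between groups, including for healthcare staff.
- Keep anyone whose first diagnosis or contact came on or after that date in the exposure group they otherwise belong to (1, 2 or 3), and report these first contacts descriptively.
- If onset is not already captured, add one before/after item for the remaining responses and for the planned second wave. That wave starts six months after lockdown, so an undated rule could admit more new cases.
- For responses already received without a date, give a sensitivity analysis that reallocates respondents with unknown onset between Group 4 and their exposure group.

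The cost is a revised derivation rule, at most one survey item, and one extra analysis. Group 4 becomes somewhat smaller. A new item cannot date responses already in, so onset could stay unknown for early respondents, possibly up to about half of the expected sample. For them the sensitivity analysis gives a range, not a correction.
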